#### Economic Evaluation

Both a cost-effectiveness analysis and a cost-utility analysis will be performed from the societal perspective. The analyses will be performed according to the intention-to-treat principle. The missing cost and effect data will be imputed using multiple imputation [59]. The imputation will include variables that are related to the missing data or the outcome measure, and variables that differ at baseline between the groups. To account for the skewed distribution of costs, predictive mean matching will be used in the multiple imputation. The number of imputed datasets to be created will be determined based on the fraction of missing information [60]. 'All of the datasets will be analyzed separately, and the results of these analyses will be pooled using Rubin's rules [61]. The incremental cost effectiveness ratios (ICERs) will be calculated by dividing the differences in mean total costs between both treatment groups, by the difference in mean effects between both treatment groups. To avoid double counting, the productivity costs due to sick leave will be excluded in the ICER, with sick leave as the effect measure. The incremental cost utility ratio will be calculated by dividing the incremental costs by the difference in the quality adjusted life years between both treatment groups. To account for the typically skewed distribution of costs, bias corrected and accelerated bootstrapping (5000 replications) will be used to estimate the 95% confidence intervals around the mean cost differences, and the uncertainty surrounding the ICERs. The bootstrapped ICERs will be graphically presented in cost effectiveness planes [62]. The cost effectiveness acceptability curves will be estimated to show the probability of the intervention program to be cost effective in comparison with the usual care for a range of different ceiling ratios, thereby showing decision uncertainty [63]. To assess the robustness of results, several secondary economic analyses will be performed: (1) complete case analysis, (2) per protocol analysis, (3) analysis with costs calculated according to the friction cost approach, and (4) analysis from the health care perspective.

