Therefore, the primary objective of the current study is to conduct an economic evaluation of the care program compared to the usual care. This economic evaluation will be conducted alongside a randomized trial, as the intervention concerns a further developed version of the care program, which has not yet been subject to an effect evaluation. In addition, this construction enables the systematic collection of relevant effect and cost data under “real life” conditions. As the intervention care program targets two levels (the hospital level and the patient level), a cluster design was chosen in order to prevent contamination between the study arms. The primary outcome duration until full sustainable RTW will be assessed on the level of the individual participant. On the level of the participating hospitals, we will investigate to what extent the guidelines on convalescence recommendations are adopted, and how future implementation of the guidelines and care program can be facilitated.

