### Sample Size

We calculated the sample size needed with the method described by Hussey and Hughes [35]. Based on the previous study, we expect a hazard ratio of 1.5 on the primary outcome full sustainable RTW. To achieve a power of 0.8 with a two-tailed alpha of .05, and taking into account a dropout rate of 10%, a total of 212 patients will be needed when using the log-rank test.

With an intracluster correlation of .05, 9 clusters, and 10 time periods, the design effect is calculated to be 2.14 [35]. By multiplying the design effect by the sample size without a correction for a stepped wedge design, a sample size of 454 women is needed. Assuming that all of the hospitals will include the same amount of participants, each hospital should include approximately 50 patients (5 patients per time period per hospital).

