### Statistical Analyses

#### Effect Evaluation

All further described analyses will be performed at the patient level, according to the intention-to-treat principle. In addition, for all tests, a two-tailed significance level of *P*≤.05 will be considered statistically significant. The statistical software packages that will be used include SPSS (version 16.0) and STATA (version 11.2).

The baseline characteristics will be summarized using descriptive statistics, and compared between the experimental and control group to verify prognostic comparability. In case of coincidental and meaningful differences, these variables will be used as covariates in the further described models.

For the primary outcome, the duration of sick leave until full sustainable RTW, Cox regression analyses will be used to investigate the intervention effect. Both the crude and adjusted analyses will be performed. In the adjusted analyses, the following variables will be used as covariates: (1) hospital, to adjust for clustering (random gamma effect); (2) type of surgery performed; (3) time period, to adjust for naturally occurring changes over time irrespective of the intervention; and (4) optionally, (time period) x (intervention) interaction term, to adjust for time effects (the longer the care program is implemented, the more effective it might be).

The differences in secondary outcomes will be assessed using generalized linear longitudinal mixed models. All of the available measurements (2 weeks, 6 weeks, 12 weeks, 26 weeks, and 52 weeks) will be used, and the baseline scores will be used as covariates, as well as the hospital and the type of surgery (random effect).

To assess whether protocol deviations caused bias, a per protocol analysis will be performed, and the results will be compared to the intention-to-treat analyses. In addition, several subgroup analyses will be performed. The predefined subgroups will be: (1) hysterectomy (TAH, VH, TLH); (2) minimally invasive hysterectomy (VH, TLH); (3) abdominal hysterectomy only; and (4) laparoscopic adnexal surgery only.

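### The economic evaluation, the stated primary objective, compares unadjusted arm means with no hospital or period term, so calendar trend enters the ICER and its intervals are too narrow for a stepped wedge

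*Protocol article*

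**What the plan says.** The Introduction (Prolonged Recovery at Home) states that "the primary objective of the current study is to conduct an economic evaluation of the care program compared to the usual care". The Economic Evaluation section defines the ICER "by dividing the differences in mean total costs between both treatment groups, by the difference in mean effects between both treatment groups", and the cost-utility ratio by "dividing the incremental costs by the difference in the quality adjusted life years between both treatment groups". For uncertainty, "bias corrected and accelerated bootstrapping (5000 replications) will be used to estimate the 95% confidence intervals around the mean cost differences" and for the spread of the ICERs. The reason given is skewness of costs. The four secondary economic analyses are complete case, per protocol, friction cost and health care perspective. Hospital, time period and clustering are not mentioned in that section.

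Elsewhere the article treats all three as necessary. Under Effect Evaluation the adjusted Cox model for return to work carries a gamma frailty for hospital, type of surgery, and "time period, to adjust for naturally occurring changes over time irrespective of the intervention". Under Sample Size, with an ICC of .05, "the design effect is calculated to be 2.14".

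**The concern.** In a stepped wedge, arm is tied to both calendar time and hospital. Every patient in the first period is a control and every patient in the last is a program patient. A raw difference in arm means therefore mixes the program effect with any change over time in resource use, sick leave or quality of life, and with the chance ordering of the hospitals. A bootstrap that treats patients as independent does not see the between-hospital part of the error.

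The article itself makes such differences plausible. The hospitals were chosen to be heterogeneous (Selection of Clusters), usual care varies considerably (Usual Care), hospital stays have been shortening (Introduction), and the cost total includes surgery and hospitalization (Cost Measures).

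The cost difference, the effect difference and the acceptability curve could all partly reflect the roll-out. The effect in the ICER denominator could disagree with the trial's own adjusted return-to-work result. The Policy Implications section expects policy makers to decide on this output.

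**Working it through.** **The plan's own figures.** Events for a hazard ratio of 1.5, power 0.8, two-sided .05: 4(1.96 + 0.842)² / (ln 1.5)² = 191. Dropout of 10%: 191/0.9 = 212. Design effect: 212 × 2.14 = 453.7, so 454. These reproduce. A design effect of 2.14 corresponds to a standard error √2.14 = 1.46 times that of an individually randomised trial.

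**Layout.** From Trial Design and Sample Size: 9 hospitals, 10 two-month periods, 5 patients per cell, one hospital crossing per period from the second. This gives 45 program and 45 control cells, or 225 patients per arm.

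- Mean period: control 165/45 = 3.67, program 330/45 = 7.33. The gap is 3.67 periods, or 7.3 months.
- Hospital shares: the first to cross supplies 9/45 = 20% of program and 1/45 = 2% of control patients; the last to cross is the reverse.

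**Variance of the crude difference** (total variance 1, ICC ρ). A hospital with x program periods enters the difference with weight (2x − 10)/45. The squared numerators for x = 9, …, 1 sum to 240. Hence

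true variance = ρ × 240/2025 + (1 − ρ) × 2/225.

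An independent-patient bootstrap estimates about 2/225 = .00889.

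| ICC | true variance | SE ratio | nominal 95% interval excludes zero |
|---|---|---|---|
| 0 | .00889 | 1.00 | 5.0% |
| .01 | .00999 | 1.06 | 6.4% |
| .02 | .01108 | 1.12 | 7.9% |
| .05 | .01437 | 1.27 | 12.3% |
| .10 | .01985 | 1.49 | 19.0% |

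At ICC .05 the true SE is 0.120 SD against 0.094 reported. The probability of being cost-saving then falls above 95% or below 5% in 2 × [1 − Φ(1.645/1.27)] = 20% of null trials, instead of 10%.

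**Calendar trend.** A linear trend of d per period shifts the crude difference by 3.67d. The share of null trials whose interval excludes zero is:

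| trend per period (assumed) | bias | ICC 0 | ICC .05 |
|---|---|---|---|
| 0.02 SD | 0.073 SD | 12% | 19% |
| 0.05 SD | 0.183 SD | 49% | 50% |

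**Simulation with skewed costs at ICC .05.** Gamma costs with a BCa interval (1,500 trials, 1,000 replicates) gave 13.1%, 18.3% and 52.3% false findings at trends of 0, 0.02 and 0.05 SD. Lognormal costs with a percentile bootstrap (3,000 trials, 500 resamples) gave 13.5%, 20.3% and 50.7%.

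**With hospital and period terms.** The estimate is unbiased under these trends. In the simulations least squares with both terms had 3.8–5.1% error, and a within-hospital bootstrap that refits that model about 4–7%. The price is precision, shown here at ICC .05, where the variance of a cell mean is .95/5 = .19:

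- Random hospital effect (Hussey and Hughes): 9 × .19 × (.19 + 10 × .05) / (120 × .19 + 660 × .05) = 1.1799/55.8 = .02115. The SE is 0.145, or 1.54 times 0.094. The implied design effect is .02115/.00889 = 2.38. The plan's 2.14 matches the closed-form factor 0.2379 multiplied by 9; multiplied by the 10 periods it gives 2.38.
- Fixed hospital effects: 90 × .19/660 = .0259. The SE is 0.161, or 1.71 times 0.094.

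**The case against.** The strongest reply is that the section never says unadjusted, and names no resampling unit. Dividing a mean cost difference by a mean effect difference is the generic definition of an ICER, which model-adjusted differences also satisfy. The Effect Evaluation sentence "All further described analyses will be performed at the patient level, according to the intention-to-treat principle" does not settle it either, since it also covers the Cox model, which has a hospital frailty. A fuller analysis plan may add adjustment. This is fair as to wording. But the section fixes the imputation method, pooling, bootstrap type, number of replications, treatment of double counting and four robustness analyses. It gives skewness as the sole reason for the bootstrap, and hospital and period appear nowhere. Read as written, it is an estimator for an individually randomised trial.

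The baseline covariates offered for chance imbalance do not help. Prognostic Factors lists sociodemographic, personal and work-related items, with severe complications if unequally distributed, but neither hospital nor period.

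Several points limit the size and stand:

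- The ICC of .05 was planned for return to work; no ICC is given for costs or QALYs.
- The trends are illustrations. A trend of 0.05 SD per period is 0.45 SD from first to last period, and nothing in the article indicates that size.
- Cost Measures converts costs to 2014 prices and uses guideline prices where available. That removes general inflation and much of the price difference between hospitals; differences and changes in resource use remain.
- Because the order is randomised, hospital mix causes no expected bias. It distorts the realised estimate and adds variance that the bootstrap misses. Only calendar trend is a systematic bias.
- The shortfall of the crude interval itself is 1.27. The factors 1.54 and 1.71 describe the wider interval of a different, adjusted estimator.

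**Conclusion.** The concern holds. The economic analysis as stated does not fit the design, on the trial's declared primary objective. If the planning ICC of .05 applies to costs, a nominal 95% interval covers about 87–88% and the false-finding rate is about 12–13%; the analytic range is 6.4% at ICC .01 to 19% at ICC .10. Any calendar trend adds a bias of 3.67 times its per-period size, and this does not depend on clustering. With ICC zero and no trend the intervals would be correct, but the plan's own sample size and Cox model assume neither.

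The figures assume equal cells of 5 patients and a hospital effect that is constant over time. The same reasoning applies to sick-leave days and QALYs, with sizes that depend on their own ICC and trend. This should be settled before analysis; the article reports that analysis had not begun.

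**What to change.** State in the analysis plan that incremental costs, sick-leave days and QALYs are estimated from a joint regression of costs and effects with arm, hospital, time period and type of surgery. Seemingly unrelated regressions with hospital and period as fixed effects would serve; a bivariate mixed model is the alternative, with inference suited to only nine hospitals. Then:

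- use the adjusted differences in the ICERs and the cost-utility ratio;
- bootstrap by resampling patients within each hospital and refitting the model in every replicate;
- draw the cost-effectiveness plane and acceptability curve from those replicates;
- include hospital and time period in the imputation model;
- report the crude differences as descriptive only, and apply the same adjustment to the four secondary economic analyses.

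The cost is plan wording and some code, with no new data. The downside is precision: at ICC .05 the intervals are about 1.5 times (random hospital effect) to 1.7 times (fixed hospital effects) as wide as those the crude bootstrap would report.

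### The economic evaluation, the stated primary objective, is defined by differences in group means and names neither hospital nor time period, although in this stepped wedge treatment is tied to both

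*Protocol article*

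**What the plan says.** The Introduction of the protocol article (Prolonged Recovery at Home) states that "the primary objective of the current study is to conduct an economic evaluation of the care program compared to the usual care".

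Under Statistical Analyses, Economic Evaluation, the ICER is obtained by "dividing the differences in mean total costs between both treatment groups, by the difference in mean effects between both treatment groups". The cost-utility ratio is built the same way, with QALYs as the effect. For uncertainty, "bias corrected and accelerated bootstrapping (5000 replications) will be used to estimate the 95% confidence intervals around the mean cost differences", and the same bootstrap serves the ICERs. The only reason given for bootstrapping is that costs are skewed. The unit resampled is not stated. The robustness analyses are "1) complete case analysis, (2) per protocol analysis, (3) analysis with costs calculated according to the friction cost approach", followed by a health care perspective. None adds hospital or period.

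Under Effect Evaluation, the adjusted Cox model includes "hospital, to adjust for clustering (random gamma effect") and "time period, to adjust for naturally occurring changes over time irrespective of the intervention". The longitudinal models for secondary outcomes include hospital and the baseline score. That section opens with "All further described analyses will be performed at the patient level, according to the intention-to-treat principle".

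Trial Design gives nine hospitals and two-month periods. All hospitals start on usual care, one hospital crosses over at each step from the second period, and all are on the intervention by the tenth. Cost Measures converts all costs to 2014 price levels with consumer price indices.

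**The concern.** In a stepped wedge, the intervention share rises with calendar time by design. Pooling all control patients and all intervention patients and comparing the two means therefore mixes the treatment effect with whatever changed over the roll-out: surgical route, length of stay, case mix, sick-leave practice. Randomising the order of the hospitals does not remove this; a period term does. The share of intervention patients also differs sharply between hospitals, so stable differences between hospitals enter the pooled contrast as well.

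The protocol recognises both threats for return to work, where it names a term for each. It does not carry them into the analysis that answers its primary objective. The Strengths and Limitations section credits the design with within-hospital comparisons that limit confounding, but a difference in pooled means does not isolate those comparisons. At stake are the ICER, the cost-utility ratio, the cost-effectiveness plane and the acceptability curve. These could be shifted by a time trend and could look more certain than they are.

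**Working it through.** **Design inputs.** There are 9 hospitals and 10 periods of 2 months, and hospital *i* crosses over at period *i*+1 (Trial Design). Sample Size gives 5 patients per hospital per period and an ICC of .05. The protocol gives no figure for the precision of the economic analysis, but its sample-size figures reproduce:
- 191 events are needed for a hazard ratio of 1.5 at 80% power and two-sided alpha .05. The unrounded value is 190.97, and 190.97/0.9 = 212.2, against 212 stated.
- 212 × 2.14 = 453.7, against 454 stated. The 90 cells of 5 give 450 patients, used below.

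**Balance over time and hospital.** The layout has 45 control and 45 intervention cells.
- Mean period, intervention: 330/45 = 7.33. Mean period, control: 165/45 = 3.67.
- Gap: 3.67 periods, or 7.33 months.
- Intervention share by hospital: 90%, 80%, … 10% from first to last.

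**Effect of drift.** With a linear drift of *d* per period, the difference in group means shifts by 3.67*d*. The protocol gives no drift, so an assumed range, in SD per period, is shown in the table below.

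**Effect of within-hospital correlation** (total variance 1, random hospital intercept, ICC ρ, 225 patients per arm).
- Hospital weights in the crude difference: (2*k* − 10)/45, where *k* = 9, 8, … 1 is the number of intervention periods. The sum of squares is 240/2025.
- True variance: ρ × 240/2025 + (1 − ρ) × 2/225. At ρ = .05 this is 0.00593 + 0.00844 = 0.01437, SE 0.120.
- Patient-level variance, simple form: 2/225 = 0.00889, SE 0.0943. The SE ratio is 1.27 and coverage about 87.7%.
- What a patient-level bootstrap within each arm actually targets is slightly smaller, because each arm holds only nine hospitals: 2 × [0.95 + 0.05 × (1 − 285/2025)]/225 = 0.00883, SE 0.0939. The ratio is 1.28 and coverage 2Φ(1.96/1.276) − 1 = 87.5%.

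The same bootstrap calculation with no drift, over assumed ICCs:

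| ICC | True SE | Patient-level SE | Coverage of nominal 95% interval |
|---|---|---|---|
| .01 | 0.100 | 0.094 | 93.5% |
| .02 | 0.105 | 0.094 | 92.0% |
| .05 | 0.120 | 0.094 | 87.5% |
| .10 | 0.141 | 0.094 | 80.7% |

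Both effects together, at ICC .05 (simple-form SE):

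| Drift (SD per period) | Bias (SD) | Coverage |
|---|---|---|
| 0.01 | 0.037 | 86% |
| 0.02 | 0.073 | 81% |
| 0.03 | 0.110 | 73% |

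A simulation with skewed costs (1,500 trials, 400 bootstrap draws, percentile rather than BCa intervals) gave 86.4% with no drift and 72% at 0.03 SD per period.

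**Precision after adjustment.** The Hussey–Hughes variance has σ² = 0.95/5 = 0.19, τ² = 0.05, U = 45 and W = V = 285. It is 9 × 0.19 × (0.19 + 0.5) / (120 × 0.19 + 660 × 0.05) = 1.1799/55.8 = 0.0211, SE 0.145. That is 1.55 times the patient-level bootstrap SE of 0.094.

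**The case against.** The strongest reply is that this is a condensed article. A ratio of a cost difference to an effect difference is simply the definition of an ICER, and it holds equally if both differences come from an adjusted regression. The section never says that the differences are unadjusted or that individual patients are resampled. Regression terms and resampling units are often left to a fuller plan.

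Part of this stands. A reader might infer that the bootstrap is known to ignore hospital, but the documents do not support that as fact. The statement "All further described analyses will be performed at the patient level" does not settle it, because the same statement governs a Cox model with a hospital frailty. Nor would a patient-level bootstrap treat variation between hospitals as zero. That variation stays in the total variance; what is lost is the correlation within hospitals. The contrast is also not purely before-and-after: in periods 2 to 9, which hold 72 of the 90 cells, both arms run concurrently. The conversion to 2014 prices removes general inflation.

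The core is not met by these points. The section is specific about imputation, pooling, estimator, bootstrap type and number of replications, double counting and four robustness analyses, yet names neither term. The rule on covariates in Effect Evaluation covers chance differences in baseline characteristics; the imbalance in calendar time is built into the design. That section's use of baseline scores applies to the longitudinal models and does not clearly reach QALYs. The imputation wording could admit hospital and period but does not name them.

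**Conclusion.** The point holds as follows. Taken as written, the estimator for the primary objective mixes treatment with calendar time, and no listed sensitivity analysis would reveal it. The imbalance itself, 3.67 periods, follows from the planned roll-out with equal cell sizes and needs no further assumption.

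The consequences are conditional. Bias arises only if care use, case mix, sick leave or QALYs drift, and the article gives no evidence of a trend. A reader might conclude that the ICER will be biased; the documents support only that it is unprotected. The undercoverage arises if patients are resampled individually, and its size depends on an ICC for costs and QALYs that is not given. The .05 comes from the sample-size calculation for return to work. At .01 the loss is small (93.5%), at .05 material (87.5%) and at .10 serious (80.7%); each figure is below nominal. Because this concerns the stated primary objective, and the article reports that data cleaning and analysis had not begun, it should be settled before analysis.

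**What to change.** - Estimate incremental costs and effects from regression models adjusted for hospital and categorical time period. For QALYs, adjust also for baseline EQ-5D, which is already collected before surgery.
- Form the ICER, cost-utility ratio, plane and acceptability curve from those adjusted increments.
- State the resampling scheme. It should respect hospitals and keep the stepped-wedge layout, for example resampling within hospital and arm and refitting the adjusted model in each replicate. Resampling whole hospitals is not a safe substitute: there are only nine, each with its own crossover time, so every replicate would change the balance of arm and period. Resampling within hospital-by-period cells of about 5 would understate the variance by a factor of about (5 − 1)/5 = 0.8, so the choice of stratum should be justified. The small number of clusters should be acknowledged when intervals are reported.
- Name hospital, period and arm in the imputation model.

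The cost is revised analysis wording, some extra programming and wider intervals: at ICC .05 the adjusted SE is about 1.55 times that from a patient-level bootstrap of crude means. No new data are needed.
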